#### Interventions

Interventions will be conducted by an instructor with adequate qualification and experience in music teaching and dementia care. Instructors will ideally have a music therapy degree, but music educators with relevant experience and training, supervised by music therapists, may also be able to conduct singing interventions for dementia.^12^ Interventions will entail individual musical training based on singing to learn 10 randomly selected songs from a list of 20 novel songs specifically created for the purposes of this study. These songs will take into consideration adequate musical complexity, length of verses and chorus and high-frequency words for the lyrics. The structure of the complete lyrics of the song will have the following sequence (similar to popular music): first verse; second verse; chorus; repetition of the first two verses; chorus; repeat chorus; final cadence.

Participants will be randomly assigned to one of the two sequences: intensive intervention phase (two sessions per week) followed by minimal intervention phase (one session per month) or vice versa (figure 2**). They will receive individual musical training based on singing during both phases**, lasting 5 months each, with 2 months of no intervention in between. During both intervention phases, participants will learn and focus the singing practice on one novel song per month. That means a total of five novel songs will be offered in each phase. The order of the songs will be randomised across the 10 months of intervention.

The instructor will use live music by singing with the support of a harmonic instrument such as piano, keyboard, guitar or accordion to deliver the musical experiences. At all times, the instructor must provide appropriate and individualised support encouraging the participant to engage in the tasks without forcing him/her to do so. It is crucial that the instructor establishes an empathic relationship with the participant for the musical experience to be pleasant, rewarding, emotionally meaningful and conducive to learning. Each session will have a duration of 40–45 min and will be conducted according to a sequence of steps^22^ as follows:

#### Step 1: baseline mood observation

The instructor will show a set of icons (online supplemental Figure S1) to the participant to self-report his/her mood and will note the response on the Scoring Session Instructor Form (SSIF, online supplemental Form F1). If this is not possible, the instructor will complete it based on observed behavioural/gestural/verbal responses.

#### Step 2: warm up

The instructor will offer a 5 min warm-up which includes breathing exercises and vocalisations. Five breathing exercises will be performed at the beginning of the lessons to practise breathing, air dosing, as well as to promote relaxation and prepare the participant for singing. After this, vocalisations will be performed. They must be offered in a pitch range matched to the participant’s vocal range. It will entail a sequence of two vocalisations such as: (a) major thirds by ascending and descending steps, (b) perfect fifths by ascending and descending steps. The rhythmic pattern suggested is a dotted eighth note with a 16th note (online supplemental Figure S2), sung in a playful manner to promote positive mood.

#### Step 3: teaching the song

First, the instructor will introduce the new song by singing it through once. A key which is comfortable for the participant will be used in all cases. The instructor will then complete a 5-item Likert scale to describe the participant’s response (liking or disliking) to the new song based on observed behavioural/gestural/verbal responses (5-point Likert scale; Online supplemental Form F1). The instructor will then teach the song. By applying their own judgement, the instructor will decide which didactic resources and strategies are best to teach the song based on the participant’s preferred learning style and performance. The instructor might choose one of the following teaching strategies: (a) repeatedly singing the entire song together with the participant having the printed lyrics as support; (b) repeatedly singing together with the participant one line at a time until completion of the chorus first and then the verses of the song, having the printed lyrics as support; (c) without having printed lyrics, the participant will learn by imitation one line at a time or the entire song. If choosing the option of teaching one line at a time during the *intensive* intervention and one session is not enough to work on the entire song, the verses and the chorus will be learnt in two different consecutive sessions. Each line should be repeated between four and six times to provide opportunities to consolidate learning. If choosing the option of teaching one line at a time during *minimal* intervention, the instructor will begin teaching the chorus first, and if there is sufficient remaining time, will teach the verses. The instructor will offer the type and number of cues that the participant needs to successfully perform the task of learning and recalling the song. The instructor will use their own judgement to gradually decrease or increase cues and support depending on participant needs to successfully complete the singing task.

#### Step 4: singing the entire chorus

The participant will be invited to sing the entire chorus. The instructor will provide the type and amount of assistance/support as needed by the participant to successfully perform the singing task. This step should be repeated eight times.

#### Step 5: singing chorus in context

The participant will be invited to perform the entire song together with the instructor. The instructor will sing the verses solo, and the participant will sing the chorus solo. The instructor will provide support of the printed lyrics of the entire song. The participant may be inclined to join singing during the verses as well; the instructor will give space for him/her to do so. A brief musical instrumental introduction will be offered to establish the musical structure and character of the song and to orient the participant in tonality, metre, character and tempo of the song. The instructor will provide the type and amount of assistance/support as needed by the participant to successfully perform the singing task. This step should be repeated at least twice. At each song ending, instructor and participant may engage in a brief verbal exchange about the singing experience or the content of the song, which will work as a brief pause, release and distractor before repeating the full song a second time.

#### Step 6: practising previously learned new song

Starting in month two of the first musical training phase, the instructor will invite the participant to rehearse a novel song learnt in a previous month (table 2). The intervention will be conducted as described in *Step 5*.

**Table 2 T2:** Combination of songs for rehearsal (example with minimal intervention first)

(a) Minimal intervention phase						
Task	Month 1	Month 2	Month 3	Month 4	Month 5	
New song	Song 1	Song 2	Song 3	Song 4	Song 5	
Rehearse	–	Song 1	Song 2	Song 3	Song 4	
**(b) Intensive intervention phase**						
Week	Task	Month 8	Month 9	Month 10	Month 11	Month 12
1	New song	Song 6	Song 7	Song 8	Song 9	Song 10
	Rehearse	–	Song 6	Song 7	Song 8	Song 9
2	New song	Song 6	Song 7	Song 8	Song 9	Song 10
	Rehearse	–	–	Song 6	Song 6 or 7	Song 6, 7 or 8
3	New song	Song 6	Song 7	Song 8	Song 9	Song 10
	Rehearse	–	Song 6	Song 7	Song 8	Song 9
4	New song	Song 6	Song 7	Song 8	Song 9	Song 10
	Rehearse	–	–	Song 6	Song 6 or 7	Song 6, 7 or 8

This is an example with minimal intervention first. The order is reversed for those randomised to intensive first.

#### Step 7: session closure

The purpose is to relax and bring the session to closure. If the participant is available and willing to do so, he/she will choose a familiar favourite song and will sing it once together with the instructor. The instructor will provide support of printed lyrics if needed. The instructor will accompany the participant with the harmonic instrument (piano, keyboard, guitar or accordion) for the participant to accomplish this task. A comfortable tonality for the participant will be used in all cases. The instructor will decide moments of solo and tutti depending on the participant and will provide a musical context by sensitively responding to the musical and communicative expressions of the participant.

#### Step 8: final mood observation

The instructor will again use a set of icons (online supplemental Figure S1) and note the response or observed behaviour (Supplementary Form F1) to describe the participant’s final mood as in *Step 1*.

#### Step 9: session rating

After the session, the instructor will complete the remainder of the SSIF (online supplemental Form F1) to record what happened in the session, including the participant’s responses and performance, title of the intervention song, title of favourite song, duration of the session, the degree of independent evocation and SoF.^20 37^ The participant’s independent recall will be rated as follows: (a) needs full support; (b) needs intermittent support to complete each line; (c) needs support in one syllable/word per line; (d) fully independent. To record independent evocation, the instructor will indicate with an ‘X’ when the first independent recall occurs during the session, which means they will mark only one cell in the form depending on type of recall and in which repetition it occurred. If the degree of independent recall changes over the same session, the instructor will also indicate with an ‘X’ the maximum degree of independent recall where it applies. Otherwise, if remaining stable, ‘no change’ will be recorded on the SSIF.

Ratings of mood and SoF will also be analysed as outcomes (see the Behavioural outcomes section).

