**Figure 3 F3:**
[figure not shown]
Standard Protocol Items: Recommendations for Interventional Trials diagram depicting the data collection schedule. ADAS-cog, Alzheimer’s Disease Assessment Scale – Cognitive Subscale; EEG, electroencephalogram; MMSE, Mini-Mental State Examination; MT, musical training.

Randomisation will be conducted centrally at NORCE, concealed from site investigators, using block randomisation with randomly varying block size, with separate lists for each site. Once a decision on inclusion has been made, informed consent obtained and baseline data collected, the randomisation result will be revealed to the instructors through an online system. Participants and instructors cannot be blinded due to the nature of the intervention. External evaluators will remain blinded after randomisation; success of blinding will be verified at the end of each participant’s participation. Treatment fidelity (adherence and competence) will be evaluated by external raters using video recordings. This study protocol is designed and reported in accordance with the Standard Protocol Items: Recommendations for Interventional Trials 2013 statement. Ethical approval has been obtained for Norway (Regional Committee for Medical Research Ethics South East Norway, 09 September 2024, reference number: 759936) and Argentina (Mautalén Salud e Investigación, CECOM, 28 February 2025, register code 14412). As funding for Austria was obtained after the initial submission of this protocol, approval for Austria has not been sought or obtained as of July 2025. Approval for this and any other future sites will be obtained from the responsible local ethics committees prior to starting recruitment there. The trial is registered in Clinicaltrials.gov, NCT06611878. Recruitment started in December 2024; the first participant was randomised on 1 April 2025. Recruitment is estimated to continue until autumn 2026, leading to October 2027 as the anticipated date for the last outcome assessment.

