#### Assessment of intervention fidelity

External evaluators blinded to intervention type and session number will rate selected sessions at specific points of the training (last session of each month and when the instructor’s SoF rating changes). To that end, sessions will be video recorded to allow external blinded evaluators to audit the session to determine adherence to the intervention manual and competence by completing the Intervention Fidelity Form (online supplemental Form F2).

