### Outcomes

The two primary outcomes, participants’ scores on the ADAS-cog^38^ and the N400 response measured using EEG, will be assessed before and after each musical training phase (figure 3). Behavioural assessments of participants’ familiarity with the song and song performance will be conducted by the instructors in every session and by external evaluators in selected sessions at specific points of the training (last session of each month and when the instructor’s SoF rating changes). Secondary outcome measures include the behavioural assessments, participants’ self-reported mood during each intervention session and any reported adverse events.

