### Secondary outcomes

#### Behavioural outcomes: mood, SoF and singing performance

*Mood* (Step 1 and 9 in Interventions) at the beginning and end of each session will be measured on 5-point Likert scales.

SoF with the current song will be assessed using the SoF scale,^20 37^ a 6-point Likert scale. It will be completed by the instructor at the end of each session (online supplemental Form F1) and by the external evaluator after selected sessions (online supplemental Form F3). For this study, a score of 4 or above will be considered as the threshold to determine familiarity-based recognition.

*Performance* as observed by an external evaluator based on video recordings will be analysed in selected sessions using the Participant Performance Cue Indicator Form (online supplemental Form F3). It yields a score for chorus solo (range 8–32, where 32 is best) and for chorus in context (2–8, where eight is best).

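### The unblinded instructor's sense-of-familiarity (SoF) rating is a secondary outcome alongside a blinded rating on the same scale, and neither is given precedence for comparing intensities

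*Protocol article*

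**What the plan says.** All references are to the protocol article.

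- **Blinding of instructors** (Trial design and procedures): "Participants and instructors cannot be blinded due to the nature of the intervention".
- **Status of the instructor's rating** (Step 9: session rating, which describes the form the instructor completes): "Ratings of mood and SoF will also be analysed as outcomes". The sentence also covers mood; this point concerns SoF only.
- **Who assesses familiarity** (Outcomes): the assessments "will be conducted by the instructors in every session and by external evaluators in selected sessions". The selected sessions are the "last session of each month and when the instructor’s SoF rating changes". The behavioural assessments are listed as secondary outcomes.
- **The scale** (Behavioural outcomes): SoF is a 6-point scale. "It will be completed by the instructor at the end of each session", and also "by the external evaluator after selected sessions". For recognition, "a score of 4 or above will be considered as the threshold to determine familiarity-based recognition". No order of precedence between the two raters is given. For singing performance, the same section names only the external evaluator.
- **Blinding of external evaluators** (Assessment of intervention fidelity): "External evaluators blinded to intervention type and session number will rate selected sessions".
- **Analysis** (Statistical analysis): continuous outcomes are compared between the two interventions within each participant.

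**The concern.** The person who teaches the song, and who knows whether it has been taught in many sessions or one, also judges how familiar it has become to the pupil. The Interventions section asks that person to build an empathic relationship with the participant. A tendency to score higher after much shared work is plausible, and it would favour the intensive phase. In a comparison of intensities, that tendency could not be told apart from learning.

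Two structural features add to this. The number of instructor ratings per song depends on the phase. And the unblinded rating helps to decide which sessions the blinded evaluator sees.

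At stake is the session-based behavioural evidence on musical memory, in a trial that calls itself assessor-blinded and already collects a blinded rating on the same scale. With two raters and no stated precedence, the choice between them is also left open.

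**Working it through.** **1. The plan's own figure.** There is no SD, expected difference or power statement for SoF. The only sample-size figure is for ADAS-cog, and it supplies two inputs below. With SD 10, a difference of 3 and r = 0.5, the SD of the within-person difference is 10 × √(2 × (1 − 0.5)) = 10, so the standardised difference is 0.30. The normal approximation gives 87.2, that is 88. The exact paired t calculation gives 90 (power 0.804). Then 90 / 0.8 = 112.5, that is 113. The stated 90 and 113 reproduce.

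**2. Ratings per song.** One novel song is taught per month, five per phase.

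| | Intensive | Minimal |
|---|---|---|
| Sessions per song | 4 weeks (Table 2) × 2 = 8 | 1 |
| Instructor SoF ratings per song | about 8 | 1 |
| Instructor SoF ratings per phase | about 40 | 5 |
| External ratings at last session of month, per song | 1 | 1 |
| External ratings at last session of month, per phase | 5 | 5 |

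In the minimal phase the single monthly session is also the last of the month, so it is always externally rated. The fixed month-end ratings are therefore balanced: 5 + 5 = 10 per participant.

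**3. Triggered ratings.** The other external ratings are made when the instructor's SoF score changes. A song rated once has no earlier score of its own to change from. If the trigger works within a song, the extra external ratings therefore fall in the intensive phase only, and the unblinded rater decides when.

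**4. Illustration of bias.** Inputs from the document: 90 completers, r = 0.5 (stated for ADAS-cog and borrowed here), two-sided 5%. Assumed, with no source in the document: SoF SD 1.0 to 1.5, a true difference of zero, and the amount of over-rating.

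SE = SD × √(2 × (1 − r)) / √90 = SD / 9.487, which is 0.105 for SD 1.0 and 0.158 for SD 1.5.

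False-positive rate = P(|Z + shift/SE| > 1.96).

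- Shift 0.2, SD 1.0: shift/SE = 1.90, giving about 48%.
- Shift 0.2, SD 1.5: shift/SE = 1.26, giving about 24%.

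Exact paired t calculations at other shifts give 10-16% for 0.10 points, 35-65% for 0.25 and 88% to over 99% for 0.50. These show how sensitive the comparison would be. They do not show that bias of any given size will occur.

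**The case against.** The strongest reply is that no section expressly tests the instructor's SoF between intensities. The ANCOVA in Statistical analysis needs a pre-test and a post-test in each phase, and a session rating of the song being taught has no natural pre-test. Every-session ratings have another evident use, in the objectives on repetitions and cues needed for recall. The blinded rating is already among the secondary outcomes, and choosing rater, summary and time point is ordinary content for the promised statistical analysis plan.

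Much of this stands, and it is why the point is conditional on SoF being compared between intensities. It does not dispose of the point. The article positively makes the instructor's ratings an outcome, the trial's declared contrast is intensive against minimal, and a better outcome for that contrast is already collected.

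Three stronger readings are tempting and are not supported.

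- A reader might infer that repeated rating alone inflates recognition: with a 10% chance of a stray score of 4 or more, 1 − 0.9⁸ = 57% of songs would cross the threshold in eight ratings, against 10% in one. This needs a rule that any single rating of 4 counts, and eight independent ratings. The article states neither; the 10% is also invented.
- A reader might infer that the main result is compromised. ADAS-cog is administered by a blinded psychometrician and N400 is measured by EEG.
- A reader might infer that session ratings are the only SoF data to set against the N400. The section on N400 amplitudes also records SoF during the EEG recognition task, before and after each phase. That is a separate measure.

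**Conclusion.** The point holds in a limited form. The article makes an unblinded instructor's SoF rating a secondary outcome beside a blinded rating on the same scale and ranks neither. Any intensive-versus-minimal comparison that uses the instructor's scores is open to treater expectation and rests on about 8 ratings per song against 1. A comparison that uses all external ratings would still carry sessions selected by the instructor's scoring.

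The size of the bias is unknown. The 24-48% false-positive rate holds only under the assumed SD, the borrowed correlation and an over-rating of 0.2 points. The sample size is unaffected. This should be put right before analysis, but it concerns a secondary outcome only.

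**What to change.** In Step 9 and in Behavioural outcomes, state that for any comparison of intensive with minimal training the SoF outcome, both the score and the threshold of 4, is the blinded external evaluator's rating at the last session of each month: one per song in each phase. Leave out of that comparison external ratings made only because the instructor's score changed; a month-end session stays in, since it would be rated anyway. Keep the instructor's ratings for learning curves within a phase and for a sensitivity analysis labelled as unblinded, and report agreement between the two raters by phase.

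The cost is wording; no new data are needed. Fewer ratings enter the comparison (10 per participant, against about 45 from instructors). Video raters may still partly infer the phase from what they see, but they do not deliver the training.

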#### Assessment of intervention fidelity

External evaluators blinded to intervention type and session number will rate selected sessions at specific points of the training (last session of each month and when the instructor’s SoF rating changes). To that end, sessions will be video recorded to allow external blinded evaluators to audit the session to determine adherence to the intervention manual and competence by completing the Intervention Fidelity Form (online supplemental Form F2).

### Outcomes

The two primary outcomes, participants’ scores on the ADAS-cog^38^ and the N400 response measured using EEG, will be assessed before and after each musical training phase (figure 3). Behavioural assessments of participants’ familiarity with the song and song performance will be conducted by the instructors in every session and by external evaluators in selected sessions at specific points of the training (last session of each month and when the instructor’s SoF rating changes). Secondary outcome measures include the behavioural assessments, participants’ self-reported mood during each intervention session and any reported adverse events.

### Primary outcomes

#### Cognitive outcome: ADAS-cog

Before and after each musical training phase, a neuropsychological assessment battery (ADAScog)^38^ will be administered to all participants by a trained psychometrician blinded to the intervention allocation. The scale consists of items to assess the following domains: language; memory; praxis and orientation. The standard ADAS-cog includes the following 11 subtests, with a total scoring range from 0 (no impairment) to 70 (most severe impairments): word recall (0–10); commands (0–5); naming (0–5); constructional praxis (0–5); ideational praxis (0–5); orientation (0–8); word recognition (0–12); remembering word recognition test instructions (0–5); spoken language ability (0–5); comprehension of spoken language (0–5); word-finding difficulty (0–5). The ADAS-cog score is based on the number of errors made within each subtest. Two versions will be included: one administered at baseline and at the 7-month assessment; another at the 5-month and 12-month assessments. In a retest situation, the minimum clinically important difference (MCID) is 3.^39^ The ADAS-cog takes 30–35 min to administer. The total score of the ADAS-cog at the end of each intervention will be used as the *primary clinical outcome measure*, and the scores on the 11 sub-domains as secondary clinical outcomes. We aim to administer the ADAS-cog within 7 days before the first and after the last musical training session of each intervention phase.

